# Preservation of the ovarian reserve and hemostasis during laparoscopic ovarian cystectomy by a hemostatic agent versus suturing for patients with ovarian endometriosis: study protocol for randomized controlled, non-inferiority trial (PRAHA-2 trial)

**DOI:** 10.1186/s13063-021-05431-1

**Published:** 2021-07-21

**Keywords:** Endometriosis, Laparoscopic ovarian cystectomy, Ovarian reserve, Hemostatic agent, Suturing

## Abstract

**Background:**

Endometriosis (EMS) can be implanted everywhere, especially in pelvic organs. EMS can be asymptomatic, but it can result in pelvic pain and infertility by inducing local inflammation and pelvic adhesion. The prevalence of EMS is about 10% in reproductive-age women and higher in women with pelvic pain or infertility. For young patients with ovarian EMS, laparoscopic ovarian cystectomy is effective in relieving pelvic pain and preventing local recurrence. However, there is a concern that the ovarian reserve would decrease after the operation because of the removal of a part of the normal ovarian tissue and thermal damage during hemostasis, which depends on the types of hemostasis such as bipolar electrocoagulation, suturing, and the use of a hemostatic agent. In this study, we aim to evaluate the protective effect for the ovarian reserve and hemostasis between a hemostatic agent and suturing during laparoscopic ovarian cystectomy for patients with ovarian EMS.

**Methods:**

This study is a randomized controlled, non-inferiority trial, where a total of 90 patients with ovarian EMS will be randomly assigned to the experimental (hemostatic agent) and control (suturing) groups. In the control group, a barbed suture will be applied for hemostasis, whereas a hemostatic agent will be applied in the experimental group. If two methods are insufficient, bipolar electrocoagulation will be applied for complete hemostasis. As the primary endpoint, the reduction rate of serum anti- Müllerian hormone (AMH) levels reflecting the ovarian reserve will be compared between the two groups 12 weeks after surgery. As secondary endpoints, we will compare the reduction rate of AMH level 48 weeks after surgery, the time required to complete hemostasis, the success rate of hemostasis within 10 min, and adverse events associated with operation.

**Discussion:**

We expect that the protective effect for the ovarian reserve and hemostasis may be comparable between the two methods, suggesting that a hemostatic agent may be preferred considering that it is easy to use during laparoscopic ovarian cystectomy.

**Trial registration:**

ClinicalTrials.govNCT04643106. Registered on 22 November 2020

**Supplementary Information:**

The online version contains supplementary material available at 10.1186/s13063-021-05431-1.

## Introduction

### Background and rationale {6a}

Endometriosis (EMS) is a condition that endometrial tissues are present outside the uterus. The most common sites of EMS are pelvic organs and peritoneum, but it can sometimes be seen at distant sites. The prevalence of EMS is about 10% in reproductive women, and it is higher in women with dysmenorrhea or infertility (17–44%) [1]. Although some women with EMS have no symptoms, a significant number of women with EMS have several symptoms such as dysmenorrhea, dyspareunia, and chronic pelvic pain and suffer from relevant infertility and cancer because of local inflammation and adhesion by EMS in the pelvic cavity [2].

Up to now, diagnostic laparoscopy is the gold standard for histologic confirmation of EMS, but medical treatment can be considered when ovarian EMS and deep infiltrating nodules are identified on imaging studies such as ultrasonography and magnetic resonance imaging. The treatment of EMS is individualized in consideration of age, the severity of symptoms, birth plan, and so on. Initially, medical treatment using nonsteroidal anti-inflammatory drugs and hormonal agents such as oral contraceptives, progestins, and gonadotropin-releasing hormone agonists can be considered [3]. However, surgical resection of deep infiltrating nodules or ovarian cystectomy should be conducted to relieve symptoms and improve the pregnancy rate [4, 5].

Nevertheless, surgical techniques for ovarian cystectomy can affect the remaining ovarian reserve after surgery because damage to the normal ovarian tissues depends on the proficiency in surgery to leave the normal ovarian tissue as much as possible and the methods for bleeding control. Sometimes the serum level of anti-Müllerian hormone (AMH) is measured before and after surgery to estimate the ovarian reserve. In young women, especially subfertile women who want to have a baby, the serum AMH level is a valuable predictor of reproductive potential [6]. In terms of bleeding control during laparoscopic ovarian cystectomy, bipolar electrocoagulation is a traditional and easy method, but it is hard to avoid thermal damage to the normal ovarian tissue. On the other hand, suture of the ovarian tissue can induce hemostasis effectively while avoiding thermal damage. However, it can lead to ischemic damage to the ovarian tissue due to excessive suture [7].

Alternatively, recent studies have suggested that hemostasis with a hemostatic agent during laparoscopic ovarian cystectomy may be effective by showing that a hemostatic agent may be superior to bipolar electrocoagulation for protecting the ovarian reserve [8–12]. In the randomized controlled trial (RCT) of PReservation of the ovArian reserve and Hemostasis during laparoscopic ovArian cystectomy (PRAHA trial), the decline ratio of serum anti-Müllerian hormone (AMH) was greater after bipolar electrocoagulation than after the use of a hemostatic agent in patients with ovarian EMS (50.7% vs. 14.4%) despite no difference between the two methods in those with ovarian non-EMS, suggesting that a hemostatic agent instead of bipolar electrocoagulation during laparoscopic ovarian cystectomy should be considered to preserve the ovarian reserve in patients with ovarian EMS [13].

On the other hand, there is a lack of data for comparing the protective effect for the ovarian reserve between laparoscopic ovarian suturing and a hemostatic agent. Given that laparoscopic ovarian suturing may take a significant amount of time to get used to, the use of a hemostatic agent can be preferred for laparoscopic gynecologists if two methods have a similar effect to protect the ovarian reserve after laparoscopic ovarian cystectomy in patients with ovarian EMS. Thus, we designed this randomized controlled, non-inferiority trial of PReservation of the ovArian reserve, and Hemostasis during laparoscopic ovArian cystectomy by a hemostatic agent versus suturing for patients with ovarian EMS (PRAHA-2 trial), where we will compare the protective effect for the ovarian reserve and hemostasis between a hemostatic agent and laparoscopic ovarian suturing. If this study shows the similar efficacy between the two methods, we can expect that a hemostatic agent may be an alternative to suturing for protecting the ovarian reserve and hemostasis in women with ovarian EMS.

### Objectives {7}

This study aims to evaluate the protective effect for preserving the ovarian reserve and hemostasis between a hemostatic agent and suturing during laparoscopic ovarian cystectomy for patients with ovarian EMS. Thus, we will estimate the reduction rate of serum AMH levels for the ovarian reserve, the time required for complete hemostasis, andhemoglobin levels with estimated blood loss for hemostasis between the two methods.

### Trial design {8}

This is an open-label, parallel-group, randomized controlled, non-inferiority trial. Participants with ovarian EMS will be randomly assigned to the experimental (hemostatic agent) and control (suturing) groups at a 1:1 ratio. After surgical treatment of ovarian EMS, we will check the serum AMH and hemoglobin levels and ovarian volumes measured by transvaginal or transrectal ultrasonography before surgery, after 2 days, after 3 months, and after 12 months. Figure 1 shows the schema of this study.

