### Outcomes {12}

#### Primary outcome

The decline ratio of serum AMH levels 12 weeks after surgery: the decline ratio of serum AMH levels is defined as the value of (preoperative AMH levels − postoperative AMH levels)/(preoperative AMH levels). Serum AMH levels will be quantitatively measured by using an enzyme-linked immunosorbent assay.

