### Sample size {14}

The number of participants is determined on the basis of the decline ratio of serum AMH levels 3 months after surgery with a significance level of 2.5% and the test power of 80%. For patients with ovarian EMS treated with laparoscopic suturing, the decline ratio of serum AMH levels 3 months after surgery has been reported to be 24.6% (interquartile range [IQR], 11.6–37.0) in the previous study [14]. From IQR and with the assumption of a normal distribution, standard deviation (SD) was calculated to be 18.81, where SD = IQR/1.349. Although the information on confidence intervals from relevant trials is required for determining the non-inferior margin, there appears no available study for confidence intervals. In one study on the comparison of the preservation of ovarian reserve between hemostatic suturing and electrocoagulation, it was reported that there was no significant difference between the two groups with respect to a reduction rate of serum AMH 3 months after surgery (suturing group 44% ± 28% vs. electrocauterization group 58% ± 24%, *p* = 0.15) [15]. Based on the 14% difference in the rate, we have calculated appropriate numbers of participants for the non-inferior margin from 8 to 14%. The smaller the non-inferior margin, the larger the sample size. Therefore, we set the non-inferior margin at 12% for the primary outcome, which will not be applied for the secondary outcomes because of a lack of relevant references. For the statistical test on non-inferiority with a mean difference of 0, the value for the sample size (*n* = 80) is available with SD of 18.81, and a non-inferior margin of 12% between the two groups, suggesting that the number of participants of each group is estimated to be 40. Supposed that the dropout rate is 10%, the number of participants should be 90 (45 per group).

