### Assignment of interventions: allocation

#### Sequence generation {16a}

A randomization table will be made by using a reproducible website program (http://randomization.com). The table will be managed by one staff who is a gynecologist but not associated with this trial.

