### Methods for additional analyses (e.g., subgroup analyses) {20b}

A separate supporting analysis will be conducted for unilateral or bilateral ovarian EMS.

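### Laterality is neither a named randomisation stratum nor a factor in the primary AMH comparison: this leaves avoidable chance imbalance, and a pooled result says less about bilateral patients

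*Protocol article*

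**What the plan says.** All references are to the protocol article.

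- **Who is enrolled.** Inclusion criteria and Recruitment {15} admit unilateral and bilateral disease, identified by imaging. No expected mix or limit is given.
- **Primary outcome.** There is one value per patient at 12 weeks: "the decline ratio of serum AMH levels is defined as the value of (preoperative AMH levels − postoperative AMH levels)/(preoperative AMH levels").
- **Margin.** Sample size {14} states "we set the non-inferior margin at 12% for the primary outcome". It applies to all patients alike.
- **Allocation.** Sequence generation {16a} says: "A randomization table will be made by using a reproducible website program". Study setting {9} gives a 1:1 ratio across two hospitals. Neither these sections nor Implementation {16c} names a stratification factor.
- **Primary comparison.** Statistical methods {20a} gives a t test or Mann-Whitney test and a repeated-measures ANOVA, with no covariate.
- **Analysis by laterality.** Section {20b} says: "A separate supporting analysis will be conducted for unilateral or bilateral ovarian EMS". It is not tied to the margin.
- **Ultrasonography.** Trial design {8} schedules "ovarian volumes measured by transvaginal or transrectal ultrasonography before surgery, after 2 days, after 3 months, and after 12 months". Volume is not among the listed outcomes.

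**The concern.** The intervention acts on the operated ovary, but serum AMH comes from both. A woman operated on both sides may well lose a larger fraction of her serum AMH than a woman operated on one side. Laterality is therefore a plausible prognostic factor for the primary outcome, and it is known before assignment.

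Two things follow. First, if neither allocation nor analysis accounts for laterality, part of the difference between arms can come from an uneven mix of unilateral and bilateral patients. With about 40 evaluable patients per arm and a 12-point margin, a few points matter. Second, the same damage to an operated ovary may give a smaller serum decline in unilateral patients. A pooled non-inferiority result then says less about bilateral patients, yet Background {6a} frames the intended conclusion for women with ovarian endometriosis in general.

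**Working it through.** **1. The plan's own figure.** Inputs from Sample size {14}: "with a significance level of 2.5% and the test power of 80"%; "standard deviation (SD) was calculated to be 18.81, where SD = IQR/1.349"; margin 12; "For the statistical test on non-inferiority with a mean difference of 0".

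- SD: (37.0 − 11.6)/1.349 = 18.83, against 18.81 stated.
- n per arm, normal approximation: 2 × (1.960 + 0.842)² × 18.81²/12² = 38.6, so 39. With the t distribution it is 40 (power 80.4%), as stated.
- Dropout: 40/0.9 = 44.4, so 45 per arm and 90 in total.
- Standard error of the difference: 18.81 × √(2/40) = 4.21 points.

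The sample size reproduces and is not in dispute.

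**2. Chance imbalance without stratification.** Let u be the unilateral share (assumed, since the document gives none). With 45 per arm, the difference in unilateral share has SD √(2u(1 − u)/45). Exact probabilities come from the difference of two binomials. A gap of 10 points means at least 5 patients, and a gap of 20 points means at least 9.

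| u | SD of gap | P(gap ≥ 10 points) | P(gap ≥ 20 points) |
|---|---|---|---|
| 0.5 | 0.105 | 34% | 7.3% |
| 0.7 | 0.097 | 30% | 5.0% |
| 0.8 | 0.084 | 23% | 2.5% |

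**3. Effect on the primary comparison.** Shift = gap × L, where L is the extra decline in bilateral patients. Assume L = 10 to 25 points.

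- 10-point gap: 0.10 × 10 = 1.0 to 0.10 × 25 = 2.5 points.
- 20-point gap: 2 to 5 points, against a margin of 12 and a standard error of 4.2.

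The gap is as likely to favour one arm as the other, so the expected shift is zero. If the study that supplied the 18.81 also mixed lateralities, this variation is already inside that SD. It is then a removable part of the standard error, not an addition to it.

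**4. What the pooled margin means by laterality.** Let w be the operated ovary's share of preoperative serum AMH in a unilateral patient (not given; 0.4 to 0.6 assumed), and D the excess fractional loss in each operated ovary with the hemostatic agent. The pooled difference is D × [(1 − u) + u × w].

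- In a purely unilateral sample, a 12-point serum difference corresponds to D = 12/w: 24 at w = 0.5, and 30 to 20 for w = 0.4 to 0.6.
- In a mixed sample at w = 0.5, D = 12/0.75 = 16.0 (u = 0.5), 12/0.65 = 18.5 (u = 0.7) or 12/0.60 = 20.0 (u = 0.8).
- If D = 12, the pooled difference is 9.0, 7.8 or 7.2 points. With 40 per arm, non-inferiority is declared with probability 10.5%, 16.5% or 20.2%. For w from 0.4 to 0.6 the range is 13.3% to 8.1% at u = 0.5 and 27.2% to 14.5% at u = 0.8.
- If D = 16 and u = 0.5, the pooled difference is exactly 12 and the probability is 2.5%.

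**5. Precision of the planned laterality analysis.** At u = 0.7, 40 evaluable per arm splits into 28 unilateral and 12 bilateral. Power against the 12-point margin is about 65% and 32%. For the bilateral group the 95% interval has half-width 2.074 × 18.81 × √(2/12) = 15.9 points, wider than the margin itself.

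**The case against.** **The target is the patient.** Objectives {7} asks about ovarian reserve in patients, estimated by serum AMH, and the margin is on that scale. On that target a smaller serum loss in a unilateral patient really is a smaller loss. This stands.

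**Tempting reading: the untreated ovary hides harm, so the test has a false-positive rate of 10% to 20%.** The documents do not support it. The probabilities in step 4 arise when the true pooled differences are 9.0, 7.8 and 7.2 points, all inside the margin, so non-inferiority is true for the population enrolled. When the pooled difference is exactly 12, the rate is 2.5%. The figures also need a value of w that the document does not give, and an SD held at 18.81 for every mix. Nor would stratification remove the dilution.

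**Tempting reading: the laterality subgroups are biased because allocation was not stratified.** They are not. Within each subgroup the arms are still randomised. The weakness of the planned analysis is precision and the lack of a link to the margin.

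**Tempting reading: operated-ovary volume should become an outcome because it is ovary-specific.** The article does not say that each ovary is recorded separately or that volume measures reserve, and preoperative volume may include the cyst that is then removed. I do not propose it.

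**Silence is not absence.** A condensed article may omit a stratum that exists in the full protocol. That is fair. But the article does state the generator, the custodian, the ratio and the tests, and laterality appears in none of them.

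**Conclusion.** The point holds as one of efficiency and of how far the claim reaches. Laterality is known beforehand and plausibly prognostic, yet as described it enters neither the allocation nor the primary comparison. The cost is avoidable variance: a 23% to 34% chance of a gap of 10 points or more in unilateral share, worth about 1 to 2.5 points on the AMH difference for a 10-point gap, and a 2.5% to 7.3% chance of a gap of 20 points or more, worth 2 to 5 points at 20. These figures rest on an assumed unilateral share of 50% to 80% and an assumed laterality effect of 10 to 25 points.

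The planned test keeps its level for the pooled population, and there is no systematic bias toward either arm. Separately, a pooled success is weaker evidence for bilateral patients than for the sample as a whole. How much weaker cannot be fixed from the document, because neither the laterality mix nor each ovary's share of AMH is given.

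**What to change.** 1. **Allocation.** Stratify the randomisation table by unilateral or bilateral disease on preoperative imaging. If the full protocol already does this, say so.
2. **Primary comparison.** Include laterality as a factor in the AMH comparison, for example in a linear model of the 12-week decline ratio on arm and laterality, giving the difference and its confidence interval against the 12-point margin. Use the laterality recorded before assignment.
3. **Analysis by laterality.** In the analysis already planned in {20b}, report each group's AMH difference with its confidence interval beside the margin. State in advance that a pooled claim will not be extended to bilateral patients if their estimate lies beyond the margin.

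**Cost.** A second list with short blocks, and some protocol wording. The sample size stays at 90. Bilateral estimates will be imprecise (step 5), so the claim may have to be narrower. Trial status says no patient had been recruited when the article was written. If enrolment has since started, items 2 and 3 can still be fixed before outcome data are examined.

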**Fig. 1 Fig1:**
[figure not shown]
Schema of PRAHA-2 trial

## Methods: participants, interventions, and outcomes

### Study setting {9}

As a multi-center trial, the study will be conducted at Seoul National University Hospital and Dongguk University Ilsan Hospital, in the Republic of Korea. All participants will be randomly assigned with a 1:1 ratio from the two hospitals.

### Eligibility criteria {10}

#### Inclusion criteria

The inclusion criteria are as follows:

##### Informed consent

Age 19–45-year-old womenAmerican Society of Anesthesiologists Physical Status classification 1 or 2Plan of laparoscopic ovarian cystectomy for unilateral or bilateral ovarian EMS diagnosed by imaging studies such as ultrasonography0.05 ng/ml or more of serum AMH levelsRegular menstruation every 21–45 daysWritten and informed consent

#### Exclusion criteria

The exclusion criteria are as follows:
Non-EMSSuspicious disease of ovarian malignancyAge 18 and younger, 46 and olderPregnancy or breastfeedingLower than 0.05 ng/ml of serum AMH levelsHormonal therapy within recent 3 monthsConsidered as inappropriate by the researcher’s judgmentRefusal of written and informed consent

### Who will take informed consent? {26a}

Voluntary consent will be obtained in written form from all participants by the responsible party in this research: the research director or other relevant staff.

### Additional consent provisions for collection and use of participant data and biological specimens {26b}

There are provisions for the collection and use of participant data in the relevant study in the written consent.

### Interventions

#### Explanation for the choice of comparators {6b}

In laparoscopic ovarian cystectomy, not only to control bleeding, but it is also important to preserve the ovarian reserve. There are several methods to control bleeding during the operation, such as bipolar electrocoagulation, suturing, and the use of a hemostatic sealant. However, there are insufficient data to compare the effect to preserve the ovarian reserve and hemostasis between a hemostatic agent and laparoscopic suturing for patients with ovarian EMS. Therefore, this study is designed to show the similar effect of a hemostatic agent compared to laparoscopic suturing for the preservation of the ovarian reserve and hemostasis during laparoscopic ovarian cystectomy.

### Intervention description {11a}

#### Control group (suturing group)

During operation, a barbed suture will be applied to the inner surface of the ovarian parenchyme where ovarian EMS was attached.

#### Experimental group (hemostatic agent group)

During laparoscopic ovarian cystectomy, bleeding will be controlled by using a hemostatic agent (EVICEL®, Johnson and Johnson, Republic of Korea), which will be supported by Dalim Medical Corp. (Seoul, Republic of Korea).

### Criteria for discontinuing or modifying allocated interventions {11b}

If the designated methods for bleeding control are not sufficient, additional electrocoagulation using the energy device (POWERBLADE, MEDIFINE Corp. Co. Ltd., Republic of Korea) will be conducted without modification of allocation.

### Strategies to improve adherence to interventions {11c}

This item is not applicable because the intervention is conducted by a member of research investigators.

### Relevant concomitant care permitted or prohibited during the trial {11d}

The major outcome measures are the decline ratio of serum AMH levels after operation. So that taking medicine that can affect the level of AMH, such as hormonal drugs, must be carefully monitored. The patient who had taken any hormonal medication within 3 months before the operation should be excluded. However, after the operation, some people need to continue additional medical therapy to prevent the recurrence of EMS. So, it is permitted to take any hormonal medication after surgery under conditions that are completely monitored by research investigators.

